### Safety procedures and ethical approval

Studies have shown that interventions targeting women experiencing IPV can result in an escalation of violence and the participants' safety being compromised (27). Based on our past experience in recruitment of women experiencing IPV, a multi-step recruitment process has been developed, with eligibility confirmation, provision of detailed information regarding the study and informed consent occurring at a designated community center, which provides a confidential and safe space. We initially designed to contact and consent female partners first in order to offer them the opportunity to weigh the risks and benefits of participation before providing consent and allowing the research team to contact their male partner. A similar approach was successfully implemented in a study recruiting mother-in-law's of young pregnant women experiencing abuse in Bengaluru (28).

In addition, a number of steps will be taken to protect participants against an escalation in physical and psychological violence and other risks. Alcohol and violence are stigmatized behaviors in communities despite their high prevalence (29, 30). Framing the study in terms of a family well-being intervention that aims to promote the well-being of families by reducing alcohol use, family conflict and violence, and increasing communication and support between the couple, including economic benefits as has been noted in earlier studies (31). In addition, we have developed a detailed case management and referral system that includes protocols for regular check-in calls with male and female participants over the course of the first 5 days of the intervention, as well as procedures for responding to physical and emotional health needs over the course of the study. The entire study team, from study case managers to community liaisons, will be trained in the identification of cues of emotional distress and signs of alcohol withdrawal, how to provide support to and make referrals for women and men who are experiencing IPV or alcohol withdrawal, and mandatory reporting procedures. Key staff from all referral agencies for women facing domestic violence will be sensitized to the study to facilitate improved trust and response for all referrals. During working hours, a medical doctor as part of the intervention team will be available to address any medical emergencies along with a trained counselor whose contact number will be made available to the men/women participants in case of any need. For support during after working hours, both men and women living in the same community where the study is planned will be identified as community liaisons to address any adverse event. The personnel will be trained to coordinate logistics between the hospital, participants and ambulance and also escort the men in case of alcohol related problems and women in case of any physical injuries to the hospital. Furthermore, we have identified shelter for women participants to stay in times of emergency related to an escalation in IPV.

Finally, the research team will be intensively trained on ethical issues in GBV research based on a team member's direct involvement in the development of global recommendations on GBV intervention research (32). Trainings are described in depth later in this manuscript.

This study has been approved by Institutional Ethics Committee, St. John's Medical College and Hospital, Bengaluru, India. All participants will be required to give their written informed consent prior to any study procedures.

## Study procedures

### Recruitment and enrollment

Couples will be recruited through outreach at women's SHG meetings, at community health camps, and through snowball sampling. The initial plan was to recruit female partners from SHGs run by our community-based partner prior to any male partner recruitment in order to avoid coercion of female partners into the study. However, despite reassurances that the study would not inform the male partner of the female partner's prior agreement, discussions with women revealed that they often desired male partners be contacted first. Therefore the recruitment plan was adjusted and research staff will use standardized scripts to describe the study and its purpose highlighting eligibility criteria, including male partner alcohol use. Interested individuals will be asked to indicate their interest in the study to the research staff, who will invite them to complete the informed consent process and an eligibility questionnaire. Eligible individuals will then be asked to provide contact information for their partners will be subsequently recruited. Once both members of the couple are deemed eligible, the couple will be enrolled in the study.

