While Standard WHO questions (26) on violence have been reliably used to measure violence in low and middle-income countries, no studies were identified that clearly documented procedures for screening out women experiencing severe violence whose risk may be increased by a couples-level violence prevention intervention. Following a risk averse model, the study team initially defined severe violence as the following types of violence occurring in the past two years: (a) being hit with a fist or something else that could hurt you on purpose, (b) being kicked, dragged, or beaten up on purpose, (c) being choked or burnt on purpose, and (d) being threatened or abused with a gun, knife, or other weapon. However, upon further discussion with stakeholders, our community-based partner, and pre-testing of the screening tool, we realized that these criteria would exclude most women experiencing violence and thus limit our ability to reach women in need of the intervention. As such, our screen-out criteria were adjusted to exclude women being kicked, dragged, or beaten up on purpose six or more times in the past 6 months, or those who were choked, burnt on purpose, threatened or abused with a gun, knife, or other weapon at any time in the past 6 months. Ever being hurt badly enough to require medical attention remained an exclusion criterion. All women who are screened out will receive access to referral resources for violence. In summary, the participant eligibility criteria include the following: (1) female partner between 18 and 40, (2) married, (3) speaks Kannada, (4) female partner reports male partner has a drinking problem, (5) female partner ever experienced psychological violence, and or physical, or sexual violence perpetrated by their male partner less than six times in the previous 6 months, and (6) both partners willing and able to enroll. Couples will be excluded if (1) the male partner is deemed to be severely alcohol dependent or at risk of severe alcohol withdrawal symptoms; (2) the female partner reported occurrences of severe physical or sexual violence characterized by attempting to choking or burning and threaten to use or actually used a knife or other sharp weapons against her or ever hurt badly enough that required medical attention; or (3) one or both members of the couple feared the counseling sessions may increase violence. Additional details regarding eligibility determination are described later.

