## Discussion

This protocol describes a pilot RCT of a novel intervention designed to reduce male alcohol use and IPV in an urban slum in India. The intervention, which was designed to build on evidence from the fields of behavioral economics and psychology, combines financial incentives and CBT to address and measure IPV in a way that, to our knowledge, has not previously been tested in low-income settings. While studies in low-income settings have tested both financial incentives and CBT, respectively for alcohol use and IPV, these interventions have yet to be tested in combination in these settings (9–11, 13, 20, 21).

The intention of the pilot is to identify lessons learned for the conduct of a full-scale RCT. With this in mind, procedures were designed to mimic those that would be used in the follow-on study. Critical safety procedures, including methods of describing the study's intention in the community, measures to screen individuals who may not benefit from the intervention, measures to minimize coercion of women during recruitment of couples, and a system of staff training and case management designed to capture and respond to all possible instances of harm were included. During study design, the adaptation of some of our designed approaches was crucial to respond to community needs and reach those who would benefit from intervention. As highlighted, we adjusted recruitment methods to allow for male recruitment prior to female recruitment. We also adjusted our threshold for defining severe violence, which was used to identify women who may be put at greater risk through participation. We took care to ensure that these adaptations maintained participant safety, particularly for women, while responding to the community context and needs. Given the relative novelty of working with couples to reduce IPV in low-income settings (14), this protocol offers guidance to researchers wishing to do so safely and will contribute to the development of global best practices.

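### When the man is screened first, being asked for his wife's contact tells him he has passed, so a later refusal points largely to her answers or her choice

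*Protocol article*

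**What the plan says.** Under Recruitment and enrollment, an interested person consents and completes an eligibility questionnaire. The next step is: "Eligible individuals will then be asked to provide contact information for their partners will be subsequently recruited". The sequence ends with: "Once both members of the couple are deemed eligible, the couple will be enrolled in the study".

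The initial plan approached women before any man, "in order to avoid coercion of female partners into the study". It was changed because "discussions with women revealed that they often desired male partners be contacted first". The Discussion describes the change in these words: "we adjusted recruitment methods to allow for male recruitment prior to female recruitment". The scripts used in outreach are "standardized scripts to describe the study and its purpose highlighting eligibility criteria, including male partner alcohol use".

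Study population lists the criteria. Several rest on what the woman says in private: that her partner has a drinking problem, the type and frequency of violence, severe violence or injury needing medical care, and fear that counseling may increase violence (the man can also report this fear). For women who fail the screen, the stated provision is: "All women who are screened out will receive access to referral resources for violence".

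**The concern.** A rule that asks only eligible people for the partner's contact does different things depending on who goes first. With the woman first, it shields her: if she discloses something that excludes the couple, the process stops and staff do not ask for her husband. With the man first, the same rule tells him that he has passed before she has been asked anything. If the couple is then declined, he has reason to look to her.

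Two things are at stake. The first is the safety of women screened out for severe violence or fear, whom the exclusions are meant to protect. The second is the working of the screen itself. Exclusion 2, and the woman's part of exclusion 3, depend on her being frank. A procedure that lets her husband trace a refusal to her gives her a reason not to be. If she holds back, a couple that the protocol means to exclude may be randomized.

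**Working it through.** No arithmetic applies. The check is to follow the stated steps on each route and ask what a refusal reveals.

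**Man first, man passes, couple then declined.** He has been asked for his wife's contact, so he can take it that his own screen was passed. The grounds that remain, from Study population, are:

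| Ground for refusal | Where it comes from | What he can make of it |
|---|---|---|
| Her age, marriage, language | Facts | He knows them already and can rule them out |
| No drinking problem reported | Her answer | Points to her |
| No violence reported, or frequency at or above the limit | Her answer | Points to her |
| Severe violence, or injury needing medical care | Her answer | Points to her |
| Fear that counseling may increase violence | Either partner's answer | Points to her if he reported none |
| Unwilling to enroll | Her choice | Points to her |
| His withdrawal risk | Physician's second screen | Open only to men scoring 16 to 30 on the dependence questionnaire |

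For a man below 16 on that questionnaire, the remaining grounds he cannot rule out all lead to his wife, but they do not show which one applied. For a man scoring 16 to 30, who is waitlisted for a second medical screen, that screen is a competing explanation. The article does not say whether it comes before or after he is asked for her contact.

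**Woman first, woman fails.** She is not asked for her husband's contact. Staff do not approach him on the strength of her screen, and he receives no result to interpret. Here the rule protects her.

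**Do the other safeguards close the gap on the man-first route?**
- The confidential community center and the alternative private setting (Safety procedures; Intake process) protect what is said in the interview. They do not affect what the outcome implies.
- The reassurance about not informing the male partner (Recruitment and enrollment) concerned the woman's prior agreement under the initial plan, not her screening result.
- The check-in calls cover the first 5 days of the intervention, and the emergency shelter is described for women participants (Safety procedures). A woman who is screened out is in neither group.
- Referral resources are promised to screened-out women. Because the promise is tied to that outcome, receiving them can itself indicate it.

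None of these deals with the signal given to a man who has already passed.

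**The case against.** The strongest reply is that this is a condensed article. It does not say how a declined couple is told, and a full protocol or operating procedure may prescribe neutral wording. That is fair as far as the wording goes, and its absence is not the point here. The point is the stated rule about who is asked for contacts: neutral wording given later does not take back a pass already signaled.

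Several stronger readings are tempting, and the article does not support them.
- *Recruitment is now mostly man first.* The text says what women often wanted and that the order is allowed. It gives no frequency. Women's self-help group meetings are still a listed recruitment channel.
- *The man learns what his wife disclosed.* He learns at most that her answers or her choice probably mattered. The only criterion named as scripted is male alcohol use.
- *The rule contradicts the Discussion*, which lists "measures to minimize coercion of women during recruitment of couples" among its safety procedures. That statement is about pressure to join. The present point is about inference after a refusal, and the Discussion openly reports the change of order.
- *Baseline violence will be under-recorded.* Baseline violence is collected in a separate survey at orientation, after eligibility, so this does not follow directly.
- *Refusal is known to cost the couple money.* The incentives are explained at orientation. What the man knows about payment earlier is not stated.

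It is also true that any screen based on self-reported violence gives a woman who wants to join some reason to under-report, whichever partner goes first. A joint decision would not remove that reason. It would remove only the added one, that a refusal can be traced to her.

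**Conclusion.** The point stands in a limited form. On the man-first route that the article now allows, the contact rule signals the man's pass, and a later refusal then points largely to the wife's answers or choice. This can expose a woman who discloses severe violence or fear, and it may weaken the candor on which exclusions 2 and 3 rest.

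Three assumptions are involved: that some couples are recruited man first, that the man understands the contact request as a pass, and that a woman may foresee the consequence. The last two are reasonable inferences, not documented facts. No number of affected couples can be given, because any figure would need a refusal rate and a man-first share that the article does not state. This is a low-cost improvement to a stated safety procedure. It does not undermine the design as a whole, but it is worth making now, since the pilot's procedures are meant to mirror those of the follow-on trial.

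**What to change.** Make the rule depend on who is screened first.

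- **Man first.** Request the wife's contact without releasing his result and without making the request depend on it. Screen both partners privately, then give one couple-level decision with a standard, non-specific reason that covers all criteria, including the medical screen.
- **Woman first.** Keep the present protection: do not contact the husband if she is ineligible or does not agree. Asking everyone for partner contacts on both routes would be a mistake, because it would send staff to the husbands of women who had just disclosed severe violence.
- **Both routes.** Give violence referral information to every screened woman, so that receiving it signals nothing.

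The outreach scripts can go on stating eligibility criteria, which people need to know before they consent.

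The cost is revised recruitment wording, some extra screens of wives whose husbands turn out to be ineligible, and a later result for the man. The change reduces what a refusal reveals but does not eliminate it, since a man may still guess.

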#### Intake process

Study staff will conduct all intake processes (i.e., informed consent and screening) at the community site. In instances where participants are not comfortable coming forward at the community site, staff will meet in an alternative private setting in the community.

### Study activities by arm

After being deemed eligible, couples will be asked to come to the study office for recruitment into one of the randomized intervention arms and an orientation session targeted for their specific study arm. During orientation, all couples will (1) learn more about the study specifics, (2) learn how to use the breathalyzer, and (3) complete a baseline survey. The baseline survey will cover basic socio-demographic information, gender norms, partner communication, relationship satisfaction, alcohol use, and IPV.

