### Randomization

Participants will be randomized at the couple-level prior to the start of the intervention by a statistician using a random number generator. Their randomization assignment will be revealed during an orientation session using a sealed envelope with their study ID.

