#### Incentives arm

Couples enrolled in the incentives arm will participate in all of the activities described above for the comparison arm except that they will receive twice-daily prompts to breathe into their breathalyzer. Given our intention to combat IPV, which generally was posited to occur in the evenings when both partners are home, this pilot study incentivized sobriety in the evenings by scheduling daily breathalyzer tests in the evenings and early mornings. Couples will learn how the incentives are tied to breathalyzer scores and will be walked through a goal-setting exercise in which couples decide on goals they would like to save for such as children's education savings goals, individual savings goals, and business savings goals. Like comparison arm participants, daily and weekly activities for the incentives arm also consist of daily prompts to men to breathe into their breathalyzer via cell phone messages; however, these men will receive larger incentives for negative breathalyzer tests. Men will come in to the study office to receive their participation fees and a proportion of their breathalyzer test rewards, and will allocate another portion of the incentives to the goals they selected during the orientation session. A distinction was made between immediate rewards and long-term rewards for saving in our study design to allow men to feel that they were earning money for their behavior change that they could control, while also addressing a need to ensure the intervention contributed positively to family goals and shared financial decision-making with their female partners.

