#### Expected outcomes and results

This pilot study will provide information to determine the design of a future effectiveness trial. Specific outcomes include ability to recruit participants and retain couples across the three arms of the study. We will also assess the effects of intervention on household safety and male partner sobriety, and attitudes and behavior related to gender equality and shared household decision making. Results pertaining to outcomes will be available after the 3 month follow-up following the intervention. The study results will be presented at National and International Research meetings and published in peer reviewed scientific journals. Findings from this pilot study in favor of a follow-on trial will include the following: (1) the intervention is safe and feasible (i.e., no harmful events directly related to the intervention are detected); we are able to recruit participants in a timely manner; loss to follow-up is less than 20% overall and similar in all study arms; and no contamination is detected or if detected, appropriate design changes can be instituted; (2) data on outcomes support the impact of the intervention on alcohol use reduction and couples' communication skills; and trends in alcohol use and IPV incidence are in the direction that supports the positive impact of the intervention; and (3) qualitative evidence similarly supports the feasibility, safety and beneficial impact of the intervention. In conclusion, this study will generate important insights on a novel, urgently needed response to IPV in a high prevalence setting.

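### As written, the baseline survey falls inside the arm-specific orientation at which the allocation is revealed, and nothing places the survey before that disclosure

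*Protocol article*

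**What the plan says.** All of this is in the protocol article.

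- **Randomization.** Couples are randomized before the intervention starts: "Participants will be randomized at the couple-level prior to the start of the intervention". Disclosure comes later: "Their randomization assignment will be revealed during an orientation session using a sealed envelope with their study ID". Neither sentence places randomization or disclosure relative to the baseline survey.
- **Study activities by arm.** Eligible couples come to the study office for "an orientation session targeted for their specific study arm". The tasks listed for that session begin with learning more about the study and continue: "learn how to use the breathalyzer, and (3) complete a baseline survey". On content: "The baseline survey will cover basic socio-demographic information, gender norms, partner communication, relationship satisfaction, alcohol use, and IPV".
- **Incentives arm.** "Couples will learn how the incentives are tied to breathalyzer scores and will be walked through a goal-setting exercise". The same section later speaks of the "goals they selected during the orientation session", so the savings exercise belongs to the orientation.
- **Intake process.** Intake is described as informed consent and screening. The baseline survey is not part of it.
- **Expected outcomes and results.** One finding that would favour a follow-on trial is that "trends in alcohol use and IPV incidence are in the direction that supports the positive impact of the intervention".

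**The concern.** A baseline measure is useful because allocation cannot have influenced it. Here the answers are self-reports on drinking, violence and the relationship, from couples who cannot be blinded, on behaviours the article itself describes as stigmatized. A man who has just learned that he will be paid for negative breath tests, and has set savings goals with his wife, may describe his recent drinking differently from a man who has just learned that he is in the comparison arm. The same applies to his wife's account of conflict. The difference could go in either direction.

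At stake are the description of the arms at baseline and any change-from-baseline or baseline-adjusted reading of the alcohol and IPV trends. The survey is also the main stated measure of these outcomes before the intervention. Breathalyzer collection is described only during the intervention, and the screening instruments are described only for eligibility. An analysis plan cannot undo an order of data collection once it has happened.

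**Working it through.** **1. Order of events as the sections give it**

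| Step | Section | What is placed there |
|---|---|---|
| Consent, screening | Intake process; Study population | AUDIT-C and SADQ for men, violence questions for women |
| Randomization | Randomization | Before the intervention; not placed relative to the survey |
| Orientation | Randomization | Envelope reveals the arm |
| Orientation | Study activities by arm | Arm-targeted session; study details, breathalyzer training, then baseline survey |
| Orientation | Incentives arm | Savings goals selected; reward rules apparently explained here too |

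A session cannot be targeted to an arm until the arm is known to those running it, and couples can hardly be given arm-specific content without learning their arm. The survey is the third of three listed tasks. No section puts it before the envelope. The natural reading is disclosure first, survey second. The text does not exclude the reverse, since the list is not declared to be a sequence and opening the envelope is not one of its items.

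**2. How an arm-dependent shift would carry through**

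The article gives no figure here, so there is none to reproduce. Let s be the excess, in SD units, of reported baseline drinking or IPV in an incentive arm over the comparison arm that is due only to knowing the arm. Let r be the correlation of baseline with follow-up, with equal SDs at both times.

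- Change from baseline: bias = s.
- Baseline-adjusted contrast: bias = r × s.
- Follow-up values alone: bias = 0.

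Both s and r are assumptions. Over s = 0.1 to 0.3 and r = 0.3 to 0.7:

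- Change score: 0.10 to 0.30 SD.
- Baseline-adjusted: 0.3 × 0.1 = 0.03 SD to 0.7 × 0.3 = 0.21 SD.

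**3. Why even a modest shift could matter for a criterion of direction**

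Assume no true effect, 20 couples per arm (Sample size section), normally distributed estimates, r = 0.5, and a shift that inflates the incentive-arm baseline.

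- Change score: SE = √[2 × 2(1 − 0.5)/20] = 0.316.
- Baseline-adjusted: SE = √[2 × (1 − 0.5²)/20] = 0.274.

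The chance that the estimate points the favourable way is Φ(bias/SE), against 50% without the shift:

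| s | Change score | Baseline-adjusted |
|---|---|---|
| 0.1 | Φ(0.10/0.316) = 62% | Φ(0.05/0.274) = 57% |
| 0.3 | Φ(0.30/0.316) = 83% | Φ(0.15/0.274) = 71% |

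A shift of the opposite sign would hide a benefit to the same degree. These figures show the mechanism and do not estimate what will happen. The article does not say that either contrast will be used.

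**The case against.** The strongest reply is that the order is inferred. Both the envelope and the survey are placed within the orientation, without saying which comes first. Figure 2, which gives enrolment, allocation and data collection points, is not shown and might settle it. A condensed article may also leave the order of tasks within a visit to the full protocol. This stands as far as it goes: a reader might conclude that the baseline is certainly an unblinded, post-allocation measure, and the article does not support that certainty. It does support the weaker statement that its wording points that way and nothing in it points the other way.

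Four further limits also stand.

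- **Missing data.** A reader might infer that couples who withdraw on seeing their arm leave no pre-allocation data and must drop out of the planned comparison of those with and without missing data. They would lack the baseline survey, but they would still have AUDIT-C, SADQ and violence screening data.
- **Objective outcome.** Male sobriety, one of the named primary effect outcomes, is also measured by photo-verified breathalyzer, which a survey reporting shift cannot touch.
- **Analysis.** The Analysis section describes retention rates and descriptive statistics by arm. It specifies no change-score or baseline-adjusted contrast, and a comparison of follow-up values between arms does not use the baseline.
- **Purpose.** The stated objectives concern feasibility, the effects are preliminary, and the direction of trends is one criterion among several, including safety, recruitment, loss to follow-up, contamination and qualitative evidence.

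Separating research from intervention staff does not answer the point, because it leaves the participants unblinded.

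**Conclusion.** The point holds as a defect in how the article fixes the order of the visit. Read naturally, self-reported baseline alcohol use, IPV, gender norms and relationship satisfaction are collected after the couple knows its arm and, in the incentive arms, possibly after the savings exercise. Arm-dependent reporting could then distort the by-arm baseline description and any baseline-referenced reading of the trends used in the decision on a follow-on trial.

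The size is unknown. Whether any bias arises depends on disclosure actually coming first, on reporting differing by arm, and on the baseline survey being used in the comparison. None of this undermines the feasibility objectives, so the pilot's main purpose survives. It should be fixed, with moderate confidence; the text does not support calling it critical.

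**What to change.** State in both the Randomization and the Study activities by arm sections that each partner completes and submits the tablet baseline survey before the envelope is opened, either at intake or in a common first part of the orientation visit. Only then is the arm revealed and the arm-specific content begun. Check the order for every couple by comparing the survey timestamp with a recorded time of envelope opening. If this is already the intended order, a sentence in each section is enough.

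The survey, staff and visit stay the same. The cost is re-ordering the visit and logging one time. If orientations are organised by arm, a common first part also has to be arranged, which is a small scheduling task. Couples who then withdraw on learning their arm would have a baseline survey as well as screening data, which strengthens the assessment of differential retention.
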